#### Sample size

The sample size calculation was performed based on the primary outcome of the randomized clinical trial (caries increment at enamel and dentinal level). The calculation considered the results of a 3-year period [7, 8]. It was also taken into account an increment of approximately 10% of the sample due to some changes in the prevalence of the disease. Thus, estimating a level of significance of 0.05 with a power of 80% and a caries prevalence of about 90% [5], the number of participants was set to 409 subjects (Kelsey method), based on a 10% absolute difference between the groups, using a two-tailed test [19].

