#### Preliminary epidemiological survey

A team of four dentists received training to diagnose caries lesions using the WHO-DMFT index for permanent teeth and the dmft for primary teeth. The team received training, and inter-examiner reliability was assessed before the start of the study; sensitivity, specificity, percentage agreement and kappa statistics were recorded. Inter-examiner reliability ranged from 0.75 to 0.84 (K-Cohen) for sound teeth and from 0.82 to 0.88 for caries lesions. Intra-examiner reliability ranged from 0.82 to 0.90 for sound teeth and from 0.84 to 0.91 for caries lesions. Dental caries prevalence (dt/DT) and severity (number of lesions) were recorded for caries at the dentinal lesion level [12]. Every subject was examined using a plain mirror (Hahnenkratt, Königsbach, Germany) and the WHO CPI ballpoint probe (Asa-Dental, Milan, Italy), under standard light. No bitewing radiographs or fibre-optic trans-illumination were used.

An ad hoc prepared questionnaire assessed general health, eating habits, oral hygiene and the self-perception of oral conditions, based on previous surveys [12, 13]. The height (cm) and the weight (kg) were measured and the body mass index (BMI) was calculated. The waist circumference was also measured.

Caries was almost ubiquitarian with only 10.04% of caries-free children (dt/DT = 0). Caries severity, in both primary and permanent dentitions, was statistically significantly related to gender and waist circumference (*p* < 0.01). This preliminary epidemiological survey will allow to design the intervention trial.

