### Outcomes

The primary outcome will be the caries increment measured both at enamel and dentinal levels. The secondary outcomes will be the differences obtained comparing caries increment and the variation of plaque pH in relation to the treatment used. Furthermore, a cost-effectiveness analysis will be performed using as outcome the measurement of quality-adjusted life years (QALY) [21].

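### The sample size is said to rest on caries increment but enters the prevalence of existing caries, and 409 does not follow from the stated inputs plus the 10% uplift

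*Protocol article*

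**What the plan says.** The Sample size section states that the calculation was based on the primary outcome, caries increment at enamel and dentinal level, and that 3-year results from two cited sources were considered. The figures it then gives are "estimating a level of significance of 0.05 with a power of 80% and a caries prevalence of about 90% [5"], a 10-point absolute difference between groups, the Kelsey method, "using a two-tailed test", and a total of 409 subjects. It adds: "It was also taken into account an increment of approximately 10% of the sample due to some changes in the prevalence of the disease".

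Under Outcomes: "The primary outcome will be the caries increment measured both at enamel and dentinal levels". The Data collection, management, and analysis section defines an event at tooth level: a new lesion, progression of an existing lesion, or an affected tooth becoming filled or missing. The Clinical examination section restricts caries recording to primary and permanent molars and counts ICDAS 1 and 2 enamel lesions.

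The 90% is traced in two places. The Introduction attributes it to a recent survey in which 10% of children were caries-free. The Preliminary epidemiological survey section gives 10.04% caries-free and says how caries was scored: "Dental caries prevalence (dt/DT) and severity (number of lesions) were recorded for caries at the dentinal lesion level".

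**The concern.** The quantity that sets the sample size is not the quantity the trial compares. They differ in three respects:

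- **State or change.** The 90% counts children who already have caries. The outcome counts new or worsened lesions after baseline. A child inside the 90% may have no event, and a caries-free child may have one.
- **Threshold.** The survey counted dentinal lesions. The outcome also includes enamel lesions.
- **Unit.** The 90% is per child. The event is per tooth, in molars only.

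For a comparison of proportions, the number needed for a fixed 10-point difference depends strongly on where the control proportion lies. If the prevalence is not the control event share, the 80% power is a statement about a different comparison. This is the only power statement in the article.

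The second matter is arithmetic. The section says that about 10% was allowed for on top, yet 409 lies close to the figure obtained with no allowance.

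**Working it through.** **Inputs.** Two-sided alpha 0.05, power 80%, rate about 0.90, absolute difference 0.10, Kelsey method (all from Sample size). Equal allocation is assumed, consistent with two groups formed in permuted blocks of 2 or 4 classes. The 409 is read as a total.

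**Step 1: the plan's own figure.** Kelsey, with p̄ the mean of the two proportions:

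n per arm = (1.960 + 0.842)² × 2 × p̄(1 − p̄) / d²

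For 0.90 v 0.80, p̄ = 0.85 and p̄(1 − p̄) = 0.1275:

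n = 7.849 × 2 × 0.1275 / 0.01 = 200.15, so 201 per arm and **402 in total**.

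The stated 409 is 409 / 402 = 1.017 times this. The inputs therefore reproduce 409 to within 2% without any uplift. The survey's exact rate of 89.96% (100 − 10.04) also gives 402.

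**Step 2: add the stated uplift.** 402 × 1.1 = 442.2, rounded up to **443**. Dividing by 0.9 instead gives 447. Neither is 409.

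**Step 3: work back from 409.** If 409 contains a 10% uplift, the base is 409 / 1.1 = 372. At 0.90 v 0.80, 372 children give about 77% power, not 80%. A base of 372 at 80% power needs a different rate:

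- 0.913 v 0.813: p̄(1 − p̄) = 0.863 × 0.137 = 0.1182; n = 185.6, so 186 per arm and 372 in total; 372 × 1.1 = 409.2.
- 0.91 v 0.81: n = 189.0 (just above), so 190 per arm and 380 in total; 409 / 380 is an uplift of 7.6%.

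So, with a 10-point difference, a full 10% uplift fits 409 only at a rate near 91.3%.

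**Step 4: how far power depends on the missing input.** The article gives no control increment, event share or SD, so the control shares below are assumptions. With n = 204.5 per arm, a 10-point difference and no clustering:

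power = Φ{[d√n − 1.960√(2p̄(1 − p̄))] / √(p₁(1 − p₁) + p₂(1 − p₂))}

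Example, 0.90 v 0.80: (1.430 − 0.990) / 0.500 = 0.88, and Φ(0.88) = 0.81.

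| Assumed control share | Comparison share | N for 80% power (Kelsey, no uplift) | Power at 409 |
|---|---|---|---|
| 0.95 | 0.85 | 284 | 92% |
| 0.90 | 0.80 | 402 | 81% |
| 0.80 | 0.70 | 590 | 65% |
| 0.70 | 0.60 | 716 | 56% |
| 0.60 | 0.50 | 778 | 53% |
| 0.50 | 0.40 | 778 | 53% |

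Below 0.50 the figures mirror those above: 0.40 needs 716, 0.30 needs 590 and 0.20 needs 402.

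**The case against.** **The power may be adequate.** A reader might infer from the table that the trial is underpowered, on the view that a realistic event share lies nearer the middle of the scale than 90%. The documents do not support that. About 90% of these children already have dentinal caries, the outcome includes early enamel lesions, and any new lesion, progression, filling or loss in any molar counts. The share of children with at least one event could be near or above 0.90, where 409 would be enough. The direction of the error is unknown. This objection stands.

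**The table is not the trial's planned test.** The analysis section takes the tooth as the unit, compares increments by Mann–Whitney U and uses Cox regression with shared frailty. The table compares child-level proportions because that is the form of the article's own calculation. This also stands: the percentages show sensitivity to the missing input and are not the trial's power.

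**The uplift may be there.** A reader might infer that the 10% was simply left out of 409. The wording is too loose for that: the rate is only about 90%, the uplift is approximate, and it is tied to changes in prevalence. A rate near 91.3% would reconcile the figures. The survey value of 89.96% makes this less likely but does not exclude it.

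**Increment data may have been used.** The 3-year results are cited and a fuller protocol may hold more. That is possible, but the article is explicit about which rate entered, and that rate contradicts the basis it claims. The mismatch in the text remains.

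**Conclusion.** The point holds as a mismatch between the claimed and the actual basis of the calculation, and the statement needs correcting. The stated 80% power belongs to a comparison of 90% with 80% caries prevalence. Power for the caries increment cannot be determined from what is given. Under assumed control event shares from 0.50 to 0.95 it would range from about 53% to 92%, for a child-level two-proportion test with a 10-point difference and no clustering.

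On the arithmetic, 409 is not reproduced by a 90% rate plus a 10% uplift: those inputs give 402 before and 443 after. Whether the uplift was omitted or a slightly higher rate was used cannot be told from the text.

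Classes are randomised, so a reader might also want to scale these powers down for clustering. The article gives no intraclass correlation, so no such figure is offered. That is a separate question, and this point does not depend on it.

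**What to change.** Recalculate on the primary outcome. State the expected control-group increment (mean and SD) or event share, the unit and follow-up period it refers to, and its source among the 3-year results already cited. State the difference to be detected on that same scale. Then give the power that 409 provides, whichever way it moves. Show the base number and the uplift as two separate figures with the exact rate used, or delete the uplift claim.

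The cost is a recalculation and a rewritten Sample size section. Under Trial status, recruitment has not begun, so nothing collected is affected. Correcting the statement does not in itself require more children; whether the target should change depends on the result.

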### Interventions

After obtaining actual caries data, schools with similar numbers of schoolchildren (at least 300 subjects per school) will be selected for the preventive project. The participants will be randomized, taking as cluster the school class, allocating each class into one of the two groups of the study (Fig. 1):

(1) The first group (Xyl) will receive sugar-free gums containing 70% (w/v) Xylitol as the only sweetener

(2) The second group (Pol) will receive reduced sugared gums containing 23% (w/v) Maltitol

Both groups of children will receive a total of 6 pellets of chewing gum a day during a period of one school year (about 9 months). All chewing gums will be produced and supplied by Perfetti Van Melle SpA (Lainate, Italy). All types of chewing gums will weigh 1.4 g each and will be identical in colour, shape and taste.

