## Discussion

Dental caries continues to be one of the most prevalent human diseases worldwide. The actual skewed caries figure suggests the need of implementing effective preventive approaches, especially for high-risk groups such as children living in low socioeconomic contests [25]. The children population living in the remote valley of Zanskar in Ladakh has shown a very high caries prevalence and still no caries preventive programme at the school level has ever been implemented. Due to the lack of dental facilities in the area, a school-based preventive programme seems to be the most effective strategy to reach children. Since caries is a behaviour-related disease, especially in children, different caries-preventive measures have been proposed, such as using sugar substitutes. Sugar-free chewing gums, especially those containing Xylitol, were effectively administered to reduce caries-associated risk factors and caries lesion increment [7–9].

A randomized controlled trial is considered the most powerful study design, in which at least two interventions are contemporaneously administered to two or more groups of subjects forming the arms of the trial. The random enrolment into each arm reduces the potential risk of bias [25]. Randomization is generally performed at an individual level. However, a group-randomized design may be useful in situations where there is a presumed lack of feasibility of carrying out the intervention at the individual level or/and when researchers aim to obtain findings on the intervention effect at the group level, as it happens with the school-based intervention [26]. School-based programmes are effective strategies to improve oral health among schoolchildren, particularly among underprivileged groups of children at high caries risk [25, 27]. Promoting children’s health through schools is strongly recommended by the World Health Organization [28].

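### The 409-child sample size assumes independently randomised children although whole school classes are randomised, so the stated 80% power does not hold once outcomes correlate within classes

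*Protocol article*

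**What the plan says.** The Sample size section sets out its inputs by "estimating a level of significance of 0.05 with a power of 80% and a caries prevalence of about 90" per cent. The result is that "the number of participants was set to 409 subjects (Kelsey method), based on a 10% absolute difference between the groups, using a two-tailed test". It mentions one inflation, about 10%, and attributes it to changes in how common the disease is. It gives no ICC, class size, number of classes or design effect.

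The Interventions section fixes the unit of randomisation: "The participants will be randomized, taking as cluster the school class, allocating each class into one of the two groups of the study". The Allocation section confirms this with permuted blocks of 2 or 4 classes. The Discussion shows that the design was chosen knowingly, noting that "a group-randomized design may be useful in situations where there is a presumed lack of feasibility" of individual delivery.

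The data analysis section takes the tooth as the unit of analysis. It names a Mann–Whitney test for the increment and a Cox regression with shared frailty, without saying whether the frailty belongs to the child or the class.

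**The concern.** The sample size formula and the randomisation scheme describe two different trials. When whole classes are allocated, a comparison of arms carries between-class variation as well as between-child variation. A formula for independent individuals omits the first.

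The article gives reasons to expect some within-class correlation. The age range is 5 to 14 years and caries is scored on primary and permanent molars, so if classes group children of similar age they will differ in the teeth at risk. The teacher distributes the gum to the class, so adherence may also be shared.

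At stake is whether 80% is a true property of the design. If it is not, an inconclusive result would be judged against a sensitivity that the trial was not built to have.

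**Working it through.** **Inputs from the Sample size section:** two-sided level 0.05; power 0.80; proportions 0.90 and 0.80 (a prevalence of about 90% and "a 10% absolute difference between the groups"). Equal allocation is inferred from the block sizes of 2 or 4 classes.

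**Step 1: reproduce the plan's figure.** Kelsey, equal arms:

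n per arm = (1.960 + 0.842)² × p̄(1 − p̄) × 2 / d², with p̄ = 0.85 and d = 0.10

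= 7.849 × 0.1275 × 2 / 0.01 = 200.15, so 201 per arm and 402 in total.

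The pooled-variance (Fleiss) version gives 398. The stated 409 lies within 3% of both, so it is in substance the individually randomised sample size.

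**Step 2: power at 409 without clustering.** With n children per arm:

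Power = Φ{[0.10 − 1.96 × √(2 × 0.85 × 0.15 / n)] / √[(0.90 × 0.10 + 0.80 × 0.20) / n]}

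At n = 204.5: (0.10 − 1.96 × 0.0353) / 0.0350 = 0.88, and Φ(0.88) = 0.81.

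**Step 3: is a design effect hidden in 409?** The 10% allowance is not visible, since 402 × 1.10 = 442. If 409 already contained it, the base would be 409 / 1.10 ≈ 372, which has about 77% power even without clustering. Against the 398 needed for 80%, the slack is 409 / 398 ≈ 1.028. It is used up at ICC = 0.028 / (m − 1), where m is the class size: about 0.003 for m = 10, 0.0015 for m = 20 and 0.001 for m = 30.

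**Step 4: apply the design effect.** DE = 1 + (m − 1) × ICC; the effective total is 409 / DE, and half of it enters the Step 2 formula as n. Class size and ICC are my assumptions, with classes taken as equal in size.

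| Children per class | ICC 0.01 | ICC 0.02 | ICC 0.05 | ICC 0.10 |
|---|---|---|---|---|
| 10 | 78% | 74% | 65% | 54% |
| 20 | 74% | 68% | 53% | 38% |
| 25 | 72% | 64% | 48% | 33% |
| 30 | 70% | 62% | 44% | 30% |

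Worked case: for m = 25 and ICC 0.05, DE = 1 + 24 × 0.05 = 2.20. The effective total is 409 / 2.20 ≈ 186, or 93 per arm. Then (0.10 − 1.96 × 0.0524) / 0.0519 ≈ −0.05, and Φ(−0.05) = 0.48.

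**Step 5: minimum detectable difference.** Solving the Step 2 formula for the difference from 90% at 80% power, with 25 per class, gives about 11, 12 and 16 percentage points for ICC 0.01, 0.02 and 0.05, against the planned 10.

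These figures use a normal reference distribution. With few classes, power would be slightly lower still.

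**The case against.** The strongest objection concerns size. A reader might infer that the trial has about an even chance of detecting its target. That needs an ICC near 0.05 with 20 to 30 children per class, and the article gives neither figure. At least 300 children per school over about 10 age grades is about 30 per grade, but this equals the class size only if each grade has a single class, which is nowhere stated. With 10 per class and an ICC of 0.01, power is still 78%. This objection stands: the direction is firm, the amount is not.

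A reader might also take the table as the power of the planned analyses. It is not. It describes the child-level comparison of proportions used for sizing, whereas the analysis section works with teeth, increments and repeated examinations. This limit also stands.

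Nor does the article support the inference that clustering is ignored throughout. A shared-frailty model is meant for correlated outcomes and could address clustering if the frailty is at class level. But with the tooth as the unit, the frailty could equally be the child. In either case an analysis model cannot restore power that the sample size did not provide for.

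Two further defences fail. One is that an article may leave such details to a fuller document. Here, however, the article states the method, inputs, total and power, and these do not fit its own design. The other is that 409 might be per arm, giving about 98% power unclustered. The wording presents it as the number of participants, and the inputs give 201 per arm.

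**Conclusion.** The point holds. The 409 children are the requirement for individual randomisation, and no allowance for class randomisation can be contained in that number. The 80% claimed for the sizing comparison is lost once the ICC exceeds about 0.001 to 0.003, for classes of 30 down to 10.

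Over the assumed ranges of Step 4, every combination falls below 80%, from a loss of a few percentage points to a loss of about 50. The documents do not allow a narrower statement. The calculation itself is reproducible; what is wrong is that it was applied to a design it does not describe.

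**What to change.** In the Sample size section, replace the 80% statement with the power that 409 children deliver after the design effect 1 + (m − 1) × ICC. Beside it, give the minimum detectable difference at 80% power. State the planned number and size of classes and an assumed ICC range, so that a reader can follow the result.

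The preliminary survey may inform the ICC only as a rough proxy, and only if class membership was recorded, which its description does not show. It measured cross-sectional caries at dentine level with the WHO index, while the trial outcome is an ICDAS increment that includes enamel lesions.

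The cost is one rewritten paragraph and a less favourable stated power. With an assumed ICC range, no new data are needed. Enrolling more children is not required by this correction. Recruitment had not begun when the article was written, so the change could be made before any data were collected.

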#### Treatment

[name] will coordinate the treatment phase of the chewing gums. The subjects of both arms will be instructed to chew a total of 6 pellets for 5 min divided into 3 intakes a day (2 in the morning, 2 after the midday meal and 2 in the afternoon) [7, 8]. Thus, the total daily intake of Xylitol in the Xyl group will be 5.8 g, whilst, in the Pol group, the amount of administered Maltitol will be 1.9 g. Subjects will be instructed to use the chewing gum immediately after the main meals and snacks. Parents/guardians will not be requested to make changes in the dietary and oral hygiene habits of their children. Tooth brushing will not be allowed for at least 1 h after the chewing gum use. All subjects will receive a fluoridated toothpaste containing 1450 μg/g NaF and a manual toothbrush, which will be substituted every 3 months throughout the entire experimental period (3 years). All children will be instructed to brush their teeth twice a day (after breakfast and dinner) for 2 min using vertical movements [20].

In order to evaluate the success of the administration of chewing gum at school, teachers will receive 1 month at a time the chewing gums necessary for that period of time and will distribute the blister packs to their school class. Children will have to return their empty blister pack when receiving that for the following month. This procedure will be repeated for all experimental (chewing) period (1-year school calendar/9 months).

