The effectiveness of the treatment will be assessed for those who fully followed the protocol (per-protocol subjects). The efficacy and consequences of treatment will be also considered, calculating the event rate (ER) for each group and the number needed to treat (NNT) [24]. An event will be defined as the change of status at tooth level, i.e. the development of a new lesion or the progression of an existing lesion to a more severe level or the change of a tooth previously affected in a filled or a missing tooth during the 2-year follow-up period.

Analyses will be performed using the statistical package Stata 16.0 (Stata Corp, College Station, USA).

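### The only adherence check described, return of an empty blister pack, cannot tell chewed gum from discarded or exchanged gum and encourages disposal of leftovers

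*Protocol article*

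**What the plan says.** The Treatment section gives the check a purpose and a procedure. The purpose opens the paragraph: "In order to evaluate the success of the administration of chewing gum at school, teachers will receive 1 month at a time the chewing gums" needed for that month. Teachers then "will distribute the blister packs to their school class", and "Children will have to return their empty blister pack when receiving that for the following month". This is repeated through the school year of about nine months. No count of unused pellets, diary or observed chewing is described. The instruction is to "chew a total of 6 pellets for 5 min divided into 3 intakes a day".

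Three other places bear on this:

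- Interventions, on allocation: "The participants will be randomized, taking as cluster the school class, allocating each class into one of the two groups of the study". The same section says that the gums "will be identical in colour, shape and taste".
- Allocation: the containers carry a green or blue code. The text does not say whether each blister carries it.
- Data collection, management, and analysis: "The effectiveness of the treatment will be assessed for those who fully followed the protocol (per-protocol subjects".

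**The concern.** The procedure does not serve its stated purpose. Pellets that were chewed, thrown away, given to a sibling or traded with a friend all leave the same empty pack. The wording also prescribes the result. A child aged 5 to 14 who is told to bring back an empty pack, and who has pellets left, can comply literally only by getting rid of them. Those leftovers are the one trace of missed doses that the monthly return could have captured.

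Both missed and exchanged pellets shrink the contrast in Xylitol exposure between arms. If neither is visible, a null result cannot be separated from failed delivery, and a group of full adherers cannot be identified reliably. No later analysis plan can repair this, because the information is lost when the packs are collected.

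**Working it through.** **1. Purpose against procedure.** What an empty pack can show under each course of events:

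- All pellets chewed by the assigned child: empty pack.
- Some missed, leftovers discarded: empty pack.
- Some given to or exchanged with another child: empty pack.
- Some missed, leftovers kept: non-empty pack. This is the only informative outcome, and it is the one the instruction discourages.

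**2. Opportunity for exchange.** Allocation is by class, in permuted blocks of 2 or 4 classes. Selected schools have at least 300 pupils and the target is 409 children, so few schools may be involved and both arms may sit in the same one. The gums cannot be told apart by colour, shape or taste. If blisters carry the colour code, a whole-pack swap could be noticed; a swap of loose pellets could not.

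**3. The stated intake presupposes full chewing.** 6 × 1.4 g × 0.70 = 5.88 g Xylitol (stated 5.8 g) and 6 × 1.4 g × 0.23 = 1.93 g Maltitol (stated 1.9 g). If gum is used on all 30 days of a month, which the text does not specify, the supply is 6 × 30 = 180 pellets per child.

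**4. The plan's own sample size.** Inputs from Sample size: two-sided 0.05, 80% power, prevalence about 90%, 10-point absolute difference (read as 90% vs 80%), Kelsey method.

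n per arm = (1.96 + 0.842)² × 0.85 × 0.15 × 2 / 0.10² = 201 after rounding up, so 402 in total. The stated 409 is within 3% of this. The only increment that the section mentions is about 10% for changes in prevalence; none is stated for non-adherence or exchange.

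Power with n = 409/2 = 204.5 per arm, difference d and mean rate p̄:

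Φ{[d√n − 1.96√(2p̄(1−p̄))] / √(p₁(1−p₁) + p₂(1−p₂))}

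For 90% vs 80%: (1.430 − 0.990) / 0.500 = 0.88, so power is 81.1%.

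**5. Illustration of dilution.** The documents give no rates of missed or swapped pellets, so those below are assumptions. The effect is taken as proportional to exposure, and clustering is ignored, as in the plan's own calculation.

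- Missed Xylitol pellets, fraction m: the difference is 0.10 × (1 − m), with the comparator at 90%.
- Two-way swapping, fraction s: the comparator is 0.90 − 0.10s and Xylitol is 0.80 + 0.10s, so the difference is 0.10 × (1 − 2s). Both arms move.

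| Assumption | Rates compared | Difference (points) | Power at 409 |
|---|---|---|---|
| None | 90 vs 80 | 10 | 81.1% |
| 5% missed | 90 vs 80.5 | 9.5 | 77.5% |
| 10% missed | 90 vs 81 | 9 | 73.6% |
| 20% missed | 90 vs 82 | 8 | 64.6% |
| 30% missed | 90 vs 83 | 7 | 54.5% |
| 5% swapped | 89.5 vs 80.5 | 9 | 72.4% |
| 10% swapped | 89 vs 81 | 8 | 62.1% |
| 20% swapped | 88 vs 82 | 6 | 39.7% |

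**The case against.** The article is a condensed protocol. Pellet-count forms, pack labelling, the handling of non-empty packs and an adherence threshold may all stand in the full document, and their absence here is no fault. The word for an empty pack may simply mean a used one, and a teacher collecting packs would see leftovers. Teachers are called responsible for the treatment under Blinding, so some intakes may be supervised. All of this is fair.

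It also rules out several stronger readings that a reader might infer:

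- *The next pack is withheld unless the old one is empty.* The text says only that the return happens at the hand-out of the next pack.
- *An empty pack is scored as full adherence.* No scoring rule is given.
- *Blister returns define the per-protocol set.* The analysis section does not say so; the return is merely the only adherence information described.
- *Children hold a month of gum with no oversight.* Monthly distribution and return suggest that children hold the packs, but where packs are kept and whether chewing is watched is not stated.
- *All contamination would go unseen.* This is established for loose pellets, not for whole packs.
- *The trial will lose a given amount of power.* The rates are assumed.

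What remains does not depend on missing detail. The article states what the check is for and what it consists of, and no way of scoring an empty pack can separate chewing from disposal or exchange.

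**Conclusion.** The concern holds in a limited form. The one adherence check described cannot measure what it is meant to measure, and its wording works against the single useful signal that a pack return can give. This matters more here because both arms may share a school, the gums are indistinguishable, and effectiveness is to be judged in full adherers.

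The size of the harm cannot be derived from the documents. On the assumed rates, with a proportional effect and no clustering, power at 409 children falls from 81% to about 74% with 10% missed Xylitol pellets, and to about 72% or 62% with 5% or 10% two-way swapping. These figures show sensitivity; they are not a forecast. The point is worth correcting before the start, and the article reports that recruitment has not begun.

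**What to change.** Replace the sentence on pack return in the Treatment section with:

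> All packs, empty or not, are returned each month; the teacher counts and records the unused pellets, and the next pack is issued regardless of the count.

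Base the adherence record on the counted pellets rather than on an empty pack. This removes the reason to dispose of leftovers.

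A count can still be defeated by discarding or sharing. Where feasible, teachers should therefore also hand out the in-school intakes and tick a class sheet.

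The cost is a one-sentence change, a monthly count and a simple record sheet, with no extra staff. Observed intakes cost more: up to 5 minutes of class time each, so up to 3 × 5 = 15 minutes a day if all three were observed at school. Dose and schedule are unchanged.
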